### Sample-Size Estimates

The sample-size calculation is based on the primary endpoint: “the detection probability for each group.” The detection probability was assumed as standard treatment: 2.5%, smartphone recorder: 8.5%, single-lead device: 14.5%, based on the SPOT-AF trial (13) and a previous assessment of a simulation in the CRYSTAL-AF trial (18). Non-inferiority margin was assumed to be 2.3% conservatively based on the difference in expected detection rates between single-lead device (14.5%) and smartphone-based device (8.5%) (13, 18). First, for determining the single-lead device's superiority to standard strategy at a significance level (alpha) of 5%, power (1-beta) of 80%, and margin of 2.3%, we calculated that 108 participants are needed in each group, assuming a 10% drop-out rate. 2, to prove the single-lead monitor's non-inferiority to the event recorder with a significance level (alpha) of 5%, power (1-beta) of 80%, and margin of 2.3%, each group needs 200 patients with a 10% drop-out rate. For randomization, each group will recruit 200 participants by applying the results of the pair with the greater number of participants (Figure 1). The sample-size calculation was performed using the Power and Sample Size website (http://powerandsamplesize.com/Calculators/Compare-2-Proportions/2-Sample-Non-Inferiority-or-Superiority, accessed November 22, 2021). Because it is an intention-to-treat study, we plan to conduct analyzes including drop-out cases except which the subject wants to remove the data.

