### Study Population and Randomization

Seven tertiary hospitals with stroke units in South Korea will participate in this trial and these centers represent a full coverage of all levels of care, including state-of-art tests, monitoring, imaging equipment, the latest treatment policies of specialists, and intensive care units. All patients who first visit the department of neurology with a stroke or TIA without history of AF at the time of admission and if no AF was detected during monitoring of the hospital stay will be enrolled in this study after obtaining voluntary informed consent. In this study, by referring to the inclusion criteria used in CRYSTAL-AF (16), the minimum symptoms required for inclusion by TIA were established: speech or language deficit, weakness of an arm or leg, or hemianopsia. As an inclusion criterion, history of AF was established as a person who did not have AF at the time of admission and who had no prior AF diagnosis. A surface ECG at hospitalization will be used as the screening test to check for pre-existing AF. During the hospital stay, continuous ECG monitoring will be performed through telemonitoring. Before being discharged, all enrolled participants will be randomized to the: 1) the standard treatment group, 2) the single-lead ECG patch group, and 3) the event-recorder group. The exclusion criteria are described in Figure 1. We performed block randomization using random number generator function of Excel (Microsoft, USA). The randomization ratio is 1:1:1.

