### Statistical Analysis

The CANDLE-AF trial will use an intention-to-treat analysis that includes all participants according to randomization. It is hypothesized that, regarding the AF-detection rate, the 72-h single-patch monitoring will be superior to standard care and non-inferior to the event-recorder type of monitoring. For the baseline variables, bivariate relationships will be investigated using chi-square or Fisher's exact tests and Student's *t*-tests or Wilcoxon rank sum tests. All continuous variables will be represented as mean or median with standard deviation or interquartile range, respectively. And according to the results of the normality test performed by the Shapiro-Wilk test, the *t*-test is performed for data following the normal distribution, otherwise the Mann-Whitney U test will be performed. Categorical and dichotomized variables will be described as percentages and analyzed using Fisher's exact test.

The primary outcome will be compared between the 72-h monitoring group and each control arm using the chi-square test or Fisher's exact tests. Unadjusted outcome effect sizes will be estimated as odds ratios with 95% confidence intervals as appropriate. In addition, for the time to the first documented AF episode during the 12-month observation period, Kaplan–Meier curves will be calculated for each arm and compared using a log-rank test. Moreover, we will compare the total major adverse cardiovascular or cerebrovascular events and the rate of change from antiplatelet to anticoagulant therapy following AF detection, as well as the incidence of recurrent strokes. All analyses will evaluate the effectiveness through multivariate analysis, taking other factors into account in a progressive model. In multivariate analysis, age, hypertension, heart failure, valvular disease, history of myocardial infarction, thyroid insufficiency, obesity, chronic obstructive pulmonary disease, chronic kidney disease, and smoking, which are known independent risk factors for Afib (22–27), are planned to be used as covariate. The Statistical Package for the Social Sciences (SPSS version 26.0, IBM SPSS Statistics, Armonk, New York, USA) will be used for statistical analyses. *P* < 0.05 will be considered statistically significant.

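### Patch versus event recorder: the hypothesis is non-inferiority, but the only test listed is one of difference, which never uses the 2.3-point margin and has no stated place in the decision rule

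*Protocol article*

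**What the plan says.** All places are in the protocol article.

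- **Hypothesis** (Statistical Analysis): "the 72-h single-patch monitoring will be superior to standard care and non-inferior to the event-recorder type of monitoring". Trial Design and Primary Objectives likewise name only non-inferiority for the recorder pair.
- **Planning rates** (Sample-Size Estimates): "smartphone recorder: 8.5%, single-lead device: 14.5" (per cent).
- **Margin** (same section): "Non-inferiority margin was assumed to be 2.3% conservatively based on the difference in expected detection rates". The calculation is described as "to prove the single-lead monitor's non-inferiority to the event recorder with a significance level (alpha) of 5%, power (1-beta) of 80%, and margin of 2.3" (per cent), with the result "each group needs 200 patients with a 10% drop-out rate". Whether the 5% is one-sided or two-sided is not said.
- **Test** (Statistical Analysis): "The primary outcome will be compared between the 72-h monitoring group and each control arm using the chi-square test", with Fisher's exact test as the alternative. Effect sizes are odds ratios with 95% confidence intervals, and the significance threshold is P < 0.05.
- **Allocation** (Study Population and Randomization): "The randomization ratio is 1:1:1".

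**The concern.** The hypothesis and the test do not fit together. A chi-square or Fisher test asks whether the two detection rates differ at all. Non-inferiority asks whether the patch could be worse than the recorder by 2.3 points or more. A non-significant difference does not answer that question, and a trial can show non-inferiority without a significant difference. The odds ratio interval does not help directly, because the margin is in percentage points.

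The mismatch matters more because the plan expects the patch to be better by 6 points. On the plan's own rates, a significant patch advantage is nearly as likely as not. If one appears, the article does not say whether it is a confirmatory superiority conclusion, support for non-inferiority, or a description. In an open-label trial that order is best fixed before results are seen.

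**Working it through.** **Inputs.** Recorder 8.5%, patch 14.5%, margin 2.3 points, power 80%, 200 per group including 10% drop-out (all from Sample-Size Estimates). I use n = 180 (200 × 0.9) for evaluable patients and n = 200 if all randomised patients are analysed. P < 0.05 is taken as two-sided, the usual convention for these tests.

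**1. Reproduce the stated 200.**
Variance sum V = 0.145 × 0.855 + 0.085 × 0.915 = 0.123975 + 0.077775 = 0.20175.
n = V × (z_alpha + z_power)² / (0.06 + 0.023)².
- One-sided 5%: 0.20175 × (1.645 + 0.842)² / 0.083² = 181.1; × 1.1 = 199.2, so 200. This matches.
- One-sided 2.5%: 0.20175 × (1.960 + 0.842)² / 0.083² = 229.9; × 1.1 = 252.8. This does not match.

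The companion figure of 108 per group against standard care also reproduces at one-sided 5%: 97.5, rounded up to 98, × 1.1 = 107.8. The sample size therefore rests on one-sided 5%.

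**2. Why the listed test cannot decide non-inferiority.** Two hypothetical results with 200 per group:

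| Patch vs recorder | Difference (SE), points | Chi-square P | 90% lower limit | 95% lower limit | Against -2.3 |
|---|---|---|---|---|---|
| 17 vs 17 | 0.0 (2.79) | 1.00 | -4.6 | -5.5 | not shown |
| 25 vs 17 | 4.0 (3.06) | 0.19 | -1.0 | -2.0 | shown at either level |

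Lower limits are difference - 1.645 × SE and difference - 1.960 × SE. Both results are non-significant on the listed test, yet they give opposite answers on non-inferiority.

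**3. Power for non-inferiority by the interval.**
SE = sqrt(V/n): 0.03348 at 180 and 0.03176 at 200. Power = Phi(0.083/SE - z).

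| n per group | 90% interval (z = 1.645) | two-sided 95% interval (z = 1.960) |
|---|---|---|
| 180 | Phi(2.479 - 1.645) = 79.8% | Phi(2.479 - 1.960) = 69.8% |
| 200 | Phi(2.613 - 1.645) = 83.4% | Phi(2.613 - 1.960) = 74.3% |

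**4. Power for superiority, two-sided 5%.**
- Lower 95% limit above 0: Phi(0.06/SE - 1.960) = Phi(1.792 - 1.960) = 43.3% at 180 and Phi(1.889 - 1.960) = 47.2% at 200.
- Chi-square (pooled variance): 43.0% at 180 and 46.8% at 200. Exact enumeration gives 43.4% and 46.8%.
- Fisher's exact test, by enumeration: 36.5% at 180 and 41.1% at 200.
- 80% power would need 443 evaluable per group.

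**5. Type I error of the ordered reading.** An interval that lies above 0 also lies above -2.3. If the true difference is at or below -2.3 points, superiority can be wrongly claimed only when non-inferiority already has been. If it lies between -2.3 and 0, non-inferiority is true and superiority is wrongly claimed in at most about 2.5% of trials. The second step adds nothing to the error rate within this pair.

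**The case against.** The strongest reply has three parts.

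**An omission in a condensed article is no error.** A step from non-inferiority to superiority is commonly written in the full protocol or SAP, neither of which is shown. Planning under an assumed advantage does not oblige anyone to claim superiority, and declining a claim that has under 50% power is a defensible choice. This stands: the missing superiority step alone would not be a finding. What remains is in the text itself, namely a stated non-inferiority hypothesis paired with a stated test that cannot address it.

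**A patch advantage is not ruled out as a claim.** A reader might infer that superiority over the recorder could only be reported post hoc. The article does not support that. Its Statistical Analysis section already plans a difference test against each control arm, the recorder included. The gap is that the test is tied to no hypothesis and has no place in an order.

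**The remedy is not free at every level.** A reader might also infer that judging non-inferiority on the usual two-sided 95% interval costs nothing. It lowers power by 9 to 10 points from what one-sided 5% gives, to below the stated 80%. The level must therefore be chosen openly.

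Nor should the chance of superiority be overstated. Whichever of the two listed tests is used at two-sided 5%, superiority is more likely to be missed than shown.

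**Conclusion.** The point holds as a mismatch between hypothesis and test for the patch-versus-recorder comparison. It is minor in effort but affects how a primary comparison is decided: the 2.3-point margin drives the sample size and then disappears from the analysis. It does not hold as a statement that superiority could not be claimed.

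The sizes rest on the plan's rates of 14.5% and 8.5%, equal groups of 180 to 200, normal approximations for the interval rule, and a two-sided reading of P < 0.05. Confidence is limited because a full protocol or SAP may already contain a margin-based rule.

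**What to change.** In Statistical Analysis, replace the unassigned test against the recorder with an ordered rule:

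1. Estimate the risk difference in AF detection, patch minus event recorder, in the intention-to-treat set. Conclude non-inferiority if its lower confidence limit exceeds -2.3 points.
2. State the level. A 90% interval (one-sided 5%) matches the 200 per group and 80% power. If a two-sided 95% interval is chosen, restate the power as about 70% (180 evaluable) to 74% (200 analysed), or enlarge the groups to 230 evaluable: 253 by the plan's apparent × 1.1, or 256 by dividing by 0.9.
3. Only if non-inferiority is shown, conclude superiority if the lower limit of the two-sided 95% interval exceeds 0, or by the two-sided 5% chi-square test already planned. Name one of the two, and give the difference test against the recorder no other role.
4. State that step 3 has about 43% to 47% power by chi-square (about 36% to 41% by Fisher's exact test), so failing it does not show equality.

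**Cost:** a few sentences. With the 90% interval, no extra patients and no loss of planned power. With the 95% interval, either lower stated power or more patients.

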The single-lead ECG patch (mobiCARE-MC100 TM) allows continuous monitoring and transmission to the core laboratory and is relatively comfortable because of the lightweight design. An event recorder-type ECG device based on a smartphone (KardiaMobile systemTM) that can measure and transmit the ECG predetermined intervals has also been developed. Each of these monitoring tools has advantages and disadvantages; however, they are more likely to detect AF compared to the conventional strategy. In patients over 65 years of age with elevated CHADS-VASc score (≥ 2) without AF, REHEARSE-AF (REmote HEArt Rhythm Sampling using the AliveCor heart monitor to scrEen for Atrial Fibrillation) (11) reported a 3.9-fold increase (3.8%, 19/500 vs. 1.0%, 5/500) in the AF detection rate by using the smartphone-based event-recorder type system twice weekly over 12 months, compared to routine care. A trial comparing event-recorder-type ECG with the standard guidelines for post-stroke patients also showed superiority for AF detection (8.5% vs. 2.8%, total *n* = 588) (34).

This trial is conducted to prove that the single-lead patch monitoring device is superior to the methods in the existing guidelines and is non-inferior to the event-recorder-type device. As a design for efficient research performance, the interval of use of single-lead patch devices was determined by referring to the period of high detection rate revealed in the previous ILR study for patients with cryptogenic stroke (6). If AF can be detected noninvasively and conveniently but sensitively, physicians could have more chances to reduce the embolic event rates and improve the prognosis of stroke patients. In addition, with this trial, we plan to monitor the patients' long-term outcomes; therefore, we expect additional information on whether more AF findings will lead to better patient outcomes. We hope to suggest better monitoring guidelines for post-stroke patients to detect more AF cases.

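### The 2.3-point non-inferiority margin is justified by the patch's expected lead over the event recorder, not by the recorder's benefit over standard care, and is not shown to be conservative

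*Protocol article*

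**What the plan says.** The trial has three randomised arms (Study Population and Randomization: "The randomization ratio is 1:1:1"). It has two primary aims: the patch superior to standard care, and the patch non-inferior to the event recorder.

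Sample-Size Estimates gives the planning rates: "The detection probability was assumed as standard treatment: 2.5%, smartphone recorder: 8.5%, single-lead device: 14.5" per cent. It then gives the origin of the margin: "Non-inferiority margin was assumed to be 2.3% conservatively based on the difference in expected detection rates between single-lead device (14.5%) and smartphone-based device (8.5" per cent). The same 2.3% is used in both calculations. For superiority: "at a significance level (alpha) of 5%, power (1-beta) of 80%, and margin of 2.3%, we calculated that 108 participants are needed". For non-inferiority: "margin of 2.3%, each group needs 200 patients with a 10% drop-out rate".

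Statistical Analysis plans two contrasts for the primary outcome: "The primary outcome will be compared between the 72-h monitoring group and each control arm using the chi-square test" or Fisher's exact test. It adds Kaplan–Meier curves for every arm with a log-rank comparison. It does not name a recorder-minus-standard difference.

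The evidence that bears on the recorder's benefit stands elsewhere, in the Discussion: "A trial comparing event-recorder-type ECG with the standard guidelines for post-stroke patients also showed superiority for AF detection (8.5% vs. 2.8%, total" 588 patients). Sample-Size Estimates does not use it for the margin.

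**The concern.** A non-inferiority margin is the largest loss against the active comparator that would still be acceptable. It is anchored on what the comparator is known to gain over the alternative, here standard care. The article anchors it on the gain hoped for from the new device. By that logic, a more optimistic assumption about the patch would justify a looser margin, although the recorder's worth had not changed.

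The stake is what a positive non-inferiority result would mean. If the margin is as large as the benefit that the recorder has reliably shown, non-inferiority to the recorder does not by itself imply that the patch does better than standard care. The same holds if the recorder performs poorly in this trial: a patch can match a recorder that adds nothing. The trial has a concurrent standard arm that can settle this, but as written the non-inferiority claim does not depend on it.

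**Working it through.** **Inputs.** From Sample-Size Estimates: rates of 2.5% (standard), 8.5% (recorder) and 14.5% (patch); margin 2.3 points; alpha 5%, side not stated; power 80%; drop-out 10%. From the Discussion: 8.5% against 2.8%, 588 in total, split between arms not given. Taking 10% drop-out from 200 leaves 180 evaluable per arm.

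**1. Reproducing the plan's figures.** Unpooled normal formula, one-sided 5%:

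- Non-inferiority: n = [0.085×0.915 + 0.145×0.855] × [(1.645 + 0.842)/(0.060 + 0.023)]² = 181.06; × 1.1 = 199.2, so 200.
- Superiority with a 2.3-point superiority margin: n = [0.025×0.975 + 0.145×0.855] × [(1.645 + 0.842)/(0.120 − 0.023)]² = 97.48; × 1.1 = 107.2, so 108.

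Both stated figures reproduce at one-sided 5%. At one-sided 2.5% the numbers before drop-out would be 230 and 124.

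**2. The margin on the correct basis, planning rates.** Recorder minus standard = 8.5 − 2.5 = 6.0 points. The basis that was used, patch minus recorder, is 14.5 − 8.5 = 6.0 points. The two agree by coincidence of the assumed rates. Fraction kept = 1 − 2.3/6.0 = 62%. The sample size stays at 200.

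**3. The margin on the correct basis, cited data.** Difference = 8.5 − 2.8 = 5.7 points; fraction of the point estimate kept = 1 − 2.3/5.7 = 60%. Standard error for two independent groups = √(0.085×0.915/n₁ + 0.028×0.972/n₂).

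| Assumed recorder/standard split of 588 | SE | 95% CI (points) |
|---|---|---|
| 40/60 | 0.0202 | 1.7 to 9.7 |
| 50/50 (294 each) | 0.0189 | 2.0 to 9.4 |
| 60/40 | 0.0183 | 2.1 to 9.3 |

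The split that minimises the SE puts about 63% in the recorder group. It gives SE = (√0.0778 + √0.0272)/√588 = 0.0183 and a lower limit of 2.1. So no split of 588 into two independent groups brings the lower limit up to 2.3.

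The conclusion is sensitive to how 588 is read. If it were the number in each group, SE = √(0.1050/588) = 0.0134, the lower limit would be 5.7 − 2.6 = 3.1 points, and 2.3 would keep about 25% of it.

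**4. What non-inferiority alone would show if the recorder adds nothing.** Suppose recorder and patch both detect 2.5%, the planned standard rate. With 180 per arm, SE = √(2×0.025×0.975/180) = 0.0165. The chance of declaring non-inferiority at one-sided 5% is Φ(0.023/0.0165 − 1.645) = Φ(−0.25), about 40%. The statement would be true but would say nothing about benefit. If superiority to standard were required first, the chance would be at most the 5% of that test when standard care also detects 2.5%.

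**5. What the condition costs.** For patch against standard at the planned rates with 180 per arm, SE = √[(0.0244 + 0.1240)/180] = 0.0287.

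| Null difference | Two-sided 5% | One-sided 5% |
|---|---|---|
| 2.3 points, as in the sample-size text | Φ(0.097/0.0287 − 1.960) = 92% | Φ(0.097/0.0287 − 1.645) = 96% |
| Zero | Φ(0.120/0.0287 − 1.960) = 99% | Φ(0.120/0.0287 − 1.645) = 99% |

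**The case against.** The strongest reply is that nothing numerical follows. On the planning rates both bases give 6.0 points, so the margin, the 200 per group and the decision rule survive a corrected rationale. This stands. A reader might infer that 2.3 points is too wide or that the trial must be enlarged. The article does not support that: doubt about the size comes only from the lower limit of one cited trial, with an assumed split.

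Second, the test is not lenient at the planned rates. With 180 per arm at one-sided 5%, an observed recorder rate of 8.5% requires an observed patch rate about 2.9 points higher. If the true rates were 8.5% for the recorder and 2.5% for the patch, non-inferiority would be declared about 0.07% of the time. If the recorder's true rate were only 4.5%, it would be about 7%. So a reader who infers that a worthless patch would easily pass against an effective recorder goes too far. The weakness lies where the recorder itself gains little, as in step 4.

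Third, patch against standard is already a primary comparison, so a useless patch is tested directly. This also stands; what is missing is any link between that result and the non-inferiority claim.

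Fourth, a reader might infer that two tests at 5% inflate the overall error to nearly 10%. That needs a rule that either claim alone counts as success. The article states no such rule and joins the two aims with 'and', which can mean that both are required. Order and success rules are also commonly left to the full protocol or analysis plan, so the article's silence on them is not a fault in itself. Nor would a testing order repair a margin with the wrong basis; it addresses the separate question of how a non-inferiority result can be interpreted.

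**Conclusion.** The concern holds in a limited form. The stated rationale for the margin is wrong in kind, and the claim that it is conservative is not shown. On the planning rates the right basis gives the same 6.0 points, of which 2.3 keeps about 62%, so the sample size is untouched. On the cited recorder-versus-standard data, 2.3 points exceeds the lower 95% limit of about 2.0 (1.7 to 2.1 for splits of 40/60 to 60/40). This assumes that 588 is the total of two independent groups; if it were the size of each group, the limit would be 3.1 and the margin would lie inside it.

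The practical consequence is for interpretation. As written, non-inferiority can be declared without the patch beating standard care, with about a 40% chance if recorder and patch both detect only 2.5% (180 per arm, one-sided 5%). This is an inexpensive improvement, not a defect that invalidates the design.

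**What to change.** 1. **Sample-Size Estimates:** restate the rationale as recorder minus standard, giving the effect, its confidence limit and the fraction that 2.3 points keeps. Delete 'conservatively' and the appeal to the patch-minus-recorder difference.
2. **Statistical Analysis:** allow the non-inferiority claim only if the patch is first shown superior to standard care, each test at full alpha.
3. **Statistical Analysis:** report the randomised recorder-minus-standard difference in detection, with its confidence interval, beside the non-inferiority result. A reader can then see whether the recorder had a benefit in this trial for the patch to preserve.

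The cost is wording and one further estimate, with no extra patients. The downside is that non-inferiority cannot be claimed if superiority fails. At the planned rates with 180 per arm, that risk is about 4% to 8% against the stated 2.3% superiority margin (100% minus 96% or 92%), or about 1% against zero. The text should also say which of these two superiority tests applies, because the sample-size section uses the 2.3% margin and the planned chi-square test does not.
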